## Objective 1 -Evaluate perceptions of the I-Score intervention

### *Acceptability*

The primary outcome of this pilot study will be acceptability, as measured by the Acceptability E-scale (AES) for web-based PROMs (Tariman et al., 2011). *Acceptability* is related to how agreeable, palatable, or satisfactory an intervention is perceived to be by stakeholders (Proctor et al., 2011). It will be measured, at T1, T2, and T3, with an adapted version of the AES for administration to both patients and physicians in the study. The scale has 6 items rated on a 5-point Likert scale that varies depending on the item. Example items of the original measure include “How would you rate your overall satisfaction with this computer program?”, and “How easy was this computer program [...] for you to use?” A summary score is obtained by adding the item scores (range: 6-30). A score of at least 24 (80% of maximum) indicates high acceptability and usability, as suggested by the scale developers.

Acceptability will also be measured at T1, T2 and T3 with a variant of the Net Promoters Score (NPS) used by England’s National Health Service (NHS) and labelled the Friends and Family Test (NHS, 2014). The NPS is considered a measure of user satisfaction (Hamilton et al., 2014). A single question will be asked (“How likely are you to recommend the I-Score?”) and rated on a 5-point Likert scale (1 = Extremely unlikely, 2 = Unlikely; 3 = Neither likely nor unlikely; 4 = Likely; 5 = Extremely likely). From this measure, the percentage recommending the I-Score will be calculated (score of 4 or 5), with a success threshold of 80% or more. An NPS-type score will also be calculated by creating three groups: promoters (score of 5), passives (score of 4), and detractors (score of 1-3). Subtracting the percentage of detractors from the promoters provides the NPS. NPS scores range from -100 to 100. A positive score (> 0) will be considered good (Stirling et al., 2019), and a score of  $\geq 50$ , excellent.

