**Methods:** This 6-month study will adopt a one-arm mixed method type 3 implementation-effectiveness hybrid design and be conducted in a single clinical site, the Chronic Viral Illness Service of the McGill University Health Centre. It will be guided by tools of implementation science (e.g., frameworks, outcomes). Five HIV physicians and 30 of their HIV patients will participate. The intervention will involve having patients complete the I-Score with an adapted version of the Opal smartphone app, prior to meeting with their physician. Both the patient and the physician will have access to the I-Score results, for consideration during the clinic visits at Time 1 (T1), T2 (3 months), T3 (6 months). The implementation strategy will focus on patient and provider involvement, education, and training, as well as on promoting the intervention's adaptability. The strategy's cornerstone will be the hiring of an Application Manager to facilitate implementation. Implementation, patient, and service outcomes will be collected (T1, T2, T3). The primary outcome of this pilot study is the intervention's acceptability (target: mean scale score of 4 on 5). Qualitative data obtained through provider focus groups (T2, T3), patient interviews (T2, T3) and the Application Manager's field notes (T1-3) will serve especially to evaluate the implementation strategy and inform any methodological adaptations.

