***Your thoughts on using the I-Score***

*In this section, the questions are about your thoughts on using the I-Score measure, as completed through the Opal app.*

2. How easy was the I-Score for you to use?
  - ☐ 1—very difficult
  - ☐ 2
  - ☐ 3
  - ☐ 4
  - ☐ 5—very easy
  
3. How understandable were the questions?
  - ☐ 1—difficult to understand
  - ☐ 2
  - ☐ 3
  - ☐ 4
  - ☐ 5—easy to understand
  
4. How much did you enjoy using the I-Score?
  - ☐ 1—not at all
  - ☐ 2
  - ☐ 3
  - ☐ 4
  - ☐ 5—very much
  
5. How helpful was the I-Score in describing difficulties experienced taking HIV medication?
  - ☐ 1—very unhelpful
  - ☐ 2
  - ☐ 3
  - ☐ 4
  - ☐ 5—very helpful
  - ☐ Not applicable
  
6. Was the amount of time it took to use the I-Score acceptable?
  - ☐ 1—very unacceptable
  - ☐ 2
  - ☐ 3
  - ☐ 4
  - ☐ 5—very acceptable
  
7. How would you rate your overall satisfaction with the I-Score?
  - ☐ 1—very dissatisfied
  - ☐ 2
  - ☐ 3
  - ☐ 4
  - ☐ 5—very satisfied

8. How likely are you to recommend the I-Score?

- ☐ Extremely unlikely
- ☐ Unlikely
- ☐ Neither likely nor unlikely
- ☐ Likely
- ☐ Extremely likely

| 9. Using the I-Score seems... | Completely disagree | Disagree | Neither agree nor disagree | Agree | Completely agree |
|-------------------------------|---------------------|----------|----------------------------|-------|------------------|
| a. fitting                    | ①                   | ②        | ③                          | ④     | ⑤                |
| b. suitable                   | ①                   | ②        | ③                          | ④     | ⑤                |
| c. applicable                 | ①                   | ②        | ③                          | ④     | ⑤                |
| d. like a good match          | ①                   | ②        | ③                          | ④     | ⑤                |
| e. implementable              | ①                   | ②        | ③                          | ④     | ⑤                |
| f. possible                   | ①                   | ②        | ③                          | ④     | ⑤                |
| g. doable                     | ①                   | ②        | ③                          | ④     | ⑤                |
| h. easy                       | ①                   | ②        | ③                          | ④     | ⑤                |

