### ***Your thoughts on using the I-Score***

*These last questions are about your thoughts on using the I-Score measure, as accessed by you through the ORMS dashboard.*

- 6- How easy was the I-Score for you to use?
  - ☐ 1—very difficult
  - ☐ 2
  - ☐ 3
  - ☐ 4
  - ☐ 5—very easy
- 7- How understandable were the questions?
  - ☐ 1—difficult to understand
  - ☐ 2
  - ☐ 3
  - ☐ 4
  - ☐ 5—easy to understand
- 8- How much did you enjoy using the I-Score?
  - ☐ 1—not at all
  - ☐ 2
  - ☐ 3
  - ☐ 4
  - ☐ 5—very much

9- How helpful was the I-Score in describing difficulties experienced taking HIV medication?

- ☐ 1—very unhelpful
- ☐ 2
- ☐ 3
- ☐ 4
- ☐ 5—very helpful
- ☐ Not applicable

10- Was the amount of time it took to use the I-Score acceptable?

- ☐ 1—very unacceptable
- ☐ 2
- ☐ 3
- ☐ 4
- ☐ 5—very acceptable

11- How would you rate your overall satisfaction with the I-Score?

- ☐ 1—very dissatisfied
- ☐ 2
- ☐ 3
- ☐ 4
- ☐ 5—very satisfied

12- How likely are you to recommend the I-Score?

- ☐ Extremely unlikely
- ☐ Unlikely
- ☐ Neither likely nor unlikely
- ☐ Likely
- ☐ Extremely likely

| 13- Using the I-Score seems... | Completely disagree | Disagree | Neither agree nor disagree | Agree | Completely agree |
|--------------------------------|---------------------|----------|----------------------------|-------|------------------|
| a. fitting                     | ①                   | ②        | ③                          | ④     | ⑤                |
| b. suitable                    | ①                   | ②        | ③                          | ④     | ⑤                |
| c. applicable                  | ①                   | ②        | ③                          | ④     | ⑤                |
| d. like a good match           | ①                   | ②        | ③                          | ④     | ⑤                |
| e. implementable               | ①                   | ②        | ③                          | ④     | ⑤                |
| f. possible                    | ①                   | ②        | ③                          | ④     | ⑤                |
| g. doable                      | ①                   | ②        | ③                          | ④     | ⑤                |
| h. easy                        | ①                   | ②        | ③                          | ④     | ⑤                |

14- Using the I-Score is compatible with all aspects of my work

- ☐ Extremely disagree
- ☐ Disagree
- ☐ Somewhat disagree
- ☐ Neither agree nor disagree

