***Thank you!***

## Time 2 and Time 3 questionnaire for people living with HIV

### ***Your thoughts on using the I-Score***

*In this section, the questions are about your thoughts on using the I-Score measure, as completed through the Opal app. Please answer these questions thinking about your most recent use of the I-Score.*

1- How easy was the I-Score for you to use?

- ☐ 1—very difficult
- ☐ 2
- ☐ 3
- ☐ 4
- ☐ 5—very easy

2- How understandable were the questions?

- a. 1—difficult to understand
- b. 2
- c. 3
- d. 4
- e. 5—easy to understand

3- How much did you enjoy using the I-Score?

- a. 1—not at all
- b. 2
- c. 3
- d. 4
- e. 5—very much

4- How helpful was the I-Score in describing difficulties experienced taking HIV medication?

- a. 1—very unhelpful
- b. 2
- c. 3
- d. 4
- e. 5—very helpful
- f. Not applicable

5- Was the amount of time it took to use the I-Score acceptable?

- a. 1—very unacceptable
- b. 2
- c. 3
- d. 4
- e. 5—very acceptable

6- How would you rate your overall satisfaction with the I-Score?

- a. 1—very dissatisfied
- b. 2
- c. 3
- d. 4
- e. 5—very satisfied

7- How likely are you to recommend the I-Score?

- ☐ Extremely unlikely
- ☐ Unlikely
- ☐ Neither likely nor unlikely
- ☐ Likely
- ☐ Extremely likely

| 8- Using the I-Score seems... | Completely disagree | Disagree | Neither agree nor disagree | Agree | Completely agree |
|-------------------------------|---------------------|----------|----------------------------|-------|------------------|
| a. fitting                    | ①                   | ②        | ③                          | ④     | ⑤                |
| b. suitable                   | ①                   | ②        | ③                          | ④     | ⑤                |
| c. applicable                 | ①                   | ②        | ③                          | ④     | ⑤                |
| d. like a good match          | ①                   | ②        | ③                          | ④     | ⑤                |
| e. implementable              | ①                   | ②        | ③                          | ④     | ⑤                |
| f. possible                   | ①                   | ②        | ③                          | ④     | ⑤                |
| g. doable                     | ①                   | ②        | ③                          | ④     | ⑤                |
| h. easy                       | ①                   | ②        | ③                          | ④     | ⑤                |

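### The primary acceptability score is a raw six-item sum with a mark of 24, but one item allows an unscored Not-applicable answer, which raises the effective mark for that respondent from 4.0 to 4.8 per answered item

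*Protocol*

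**What the plan says.** The Acceptability section under Objective 1 names the Acceptability E-scale (AES) as the primary outcome, collected from patients and physicians at T1, T2 and T3. It states: "The scale has 6 items rated on a 5-point Likert scale that varies depending on the item". It then gives the scoring rule, "A summary score is obtained by adding the item scores (range: 6-30"), and the mark: "A score of at least 24 (80% of maximum) indicates high acceptability and usability, as suggested by the scale developers".

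Table 3 (cited in the text as Table 2) applies the mark to the group mean, 24 or more, for both groups at each visit. The Quantitative analysis section compares the mean at each visit with its threshold and tests the T3 mean against it with a t-test. The Summary gives the same target per item: "target: mean scale score of 4 on 5".

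The Appendix holds the four forms that collect the scale: Time 1 and Time 2/3, for patients and for physicians. In each, the item "How helpful was the I-Score in describing difficulties experienced taking HIV medication" offers the answers 1 to 5 and a sixth, unnumbered one ("f. Not applicable" in the Time 2/3 forms). No other AES item has this option.

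**The concern.** The scoring rule and the form do not fit each other. A sum with range 6 to 30 assumes six numbers per respondent, and the form allows five. If the available item scores are simply added, the total is on a shorter scale but is still averaged with the others and judged against 24.

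The two statements of the target then separate. A respondent who answers 4 on five items and Not applicable on the sixth meets the Summary's target exactly, yet contributes 20 to a mean that must reach 24. The Protocol's other multi-item perception scales (compatibility, appropriateness, feasibility) are averaged and have no such option. Only the primary scale combines a raw sum with an unscored answer.

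The result has a consequence: under Study metrics and instruments, a missed threshold means that modifications are needed before a definitive trial. The answer is also a plausible one. Eligibility looks back 12 months for adherence problems while the I-Score asks about the past 4 weeks, so an eligible patient may have no recent difficulty to describe.

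**Working it through.** **Inputs from the Protocol.** Six items scored 1 to 5; mark 24 on the group mean; Summary target 4 on 5; 30 patients and 5 physicians. **Assumed, because the Protocol gives no figure:** the mean item score m, the share f answering Not applicable, and the standard deviation (SD) of the sum. The Not-applicable answer is taken to add nothing to the sum and to be unrelated to the other five ratings.

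**1. The stated figures reproduce.** Range 6 × 1 = 6 to 6 × 5 = 30; 24/30 = 80%; 24/6 = 4.0 per item, which equals the Summary target. With all six items scored, the two metrics agree.

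**2. One item unscored.** Range 5 × 1 = 5 to 5 × 5 = 25. The mark is then 24/25 = 96% of maximum, or 24/5 = 4.8 per answered item. The five-item equivalent of the mark is 24 × 5/6 = 20. Five answers of 4 sum to 20; prorated, 20/5 × 6 = 24.

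**3. Effect on the group mean.** Mean = 6m(1 − f) + 5mf = 6m − fm. This is below 24 when f > (6m − 24)/m.

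| Assumed item mean m | Mean with all six scored | Share f above which the mean is below 24 | Patients needed, of 30 |
|---|---|---|---|
| 4.1 | 24.6 | 0.6/4.1 = 15% | 5 |
| 4.2 | 25.2 | 1.2/4.2 = 29% | 9 |
| 4.3 | 25.8 | 1.8/4.3 = 42% | 13 |
| 4.5 | 27.0 | 3.0/4.5 = 67% | 21 |

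Checks at N = 30: for m = 4.1 and 5 such patients, (25 × 24.6 + 5 × 20.5)/30 = 23.92; for m = 4.2 and 8 such patients, (22 × 25.2 + 8 × 21)/30 = 24.08, so 9 are needed.

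**4. Physicians, N = 5.** One such answer gives (4 × 24.6 + 20.5)/5 = 23.78 at m = 4.1 and 24.36 at m = 4.2. Two give 23.52 at m = 4.2 and 24.08 at m = 4.3.

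**5. The T3 test.** Mixing five- and six-item sums also adds variance f(1 − f)m². Take m = 4.3, f = 20%, N = 30 and an SD of 3.5 within each type of respondent. With all six items scored, t = (25.8 − 24)/(3.5/√30) = 2.82. With the mixture, the mean is 25.8 − 0.86 = 24.94, the variance is 12.25 + 0.2 × 0.8 × 4.3² = 15.21, and t = 0.94/(3.90/√30) = 1.32, against a one-sided 5% critical value of 1.70. At an SD of 2.5, t goes from 3.94 to just under 1.70; at an SD of 4.5, from 2.19 to 1.07. The test can therefore lose significance while the mean is still above 24.

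**The case against.** The strongest reply is that the Protocol only omits a scoring convention, which may sit in a statistical analysis plan that is not shown. This stands for the missing rule itself: its absence is not the finding. It does not dispose of the point, because the rule that is written, adding the items over a range of 6 to 30, gives a value on the wrong scale for an answer that the Protocol's own forms offer.

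Four stronger readings are tempting and are not supported:

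- *A Not-applicable respondent is scored as low acceptability.* The maximum of 25 is above 24, so sums of 24 or 25 still reach the mark. Success is also judged on the group mean, not per person.
- *Such respondents are dropped, so the result is distorted whichever way they are handled.* No text says that they are dropped. Averaging the answered items is a third possibility, it avoids the shift, and the Summary's metric already allows it.
- *The Summary contradicts the Acceptability section.* The two are identical whenever all six items are scored. They part only for the unscored answer.
- *The option will be chosen more often at T3 as barriers fall.* This presumes an effect that the study merely observes. Recruiting patients with adherence problems in the past 12 months may also make the answer less common at entry.

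It is also fair that this is a small one-arm pilot with two further acceptability measures and qualitative data, and that the scoring can be settled before analysis without loss of data.

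**Conclusion.** The point holds in a limited form. The raw-sum rule and its 6 to 30 range do not fit the response options. Applied as written, they raise the effective mark from 4.0 to 4.8 per answered item for anyone choosing Not applicable, and pull the group mean down relative to the Summary target.

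Whether this changes the result depends on two unknowns, the true item mean and the share choosing the option. The mean is vulnerable when acceptability lies just above target (15% suffices at an item mean of 4.1) and robust when it is high (about 67% is needed at 4.5). The formal T3 test is more sensitive than the mean, under the assumed SDs. All of these are scenarios, not forecasts. Severity is moderate: the outcome is primary and bears on progression, but the remedy is simple and nothing is lost if it is made before the data are analysed.

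**What to change.** Score the AES as the mean of the answered items, with a stated minimum number answered (for example 5 of 6), and set success at a mean of 4.0 or more, equivalently 6 × mean of 24 or more. Alternatively, remove the Not-applicable option from the helpfulness item in all four questionnaires. Use the one chosen metric in the Summary, the Acceptability section, Table 3 and the T3 test. If the option stays, report the number of Not-applicable answers by visit.

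The cost is one scoring sentence and aligned wording, with no new data. The downside of averaging is a small departure from the stated raw sum for respondents with one unscored item. The downside of removing the option is that some respondents must rate a question that they feel does not apply to them. If an analysis plan already contains such a rule, the Protocol text need only be brought into line with it.

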### *Appropriateness*

Appropriateness concerns the perceived fit or relevance of the intervention for the particular users, setting, or problem at hand (Proctor et al., 2011). It will be measured, at T1, T2, and T3, with two instruments. One concerns the perceived compatibility of the I-Score with the physicians’ work. The perceived compatibility of an information technology innovation broadly relates to how consistent it is perceived to be with the potential users’ values, needs, and past experiences (Moore and Benbasat, 1991). It will only be collected from providers, with a compatibility subscale developed by Moore and Benbasat (1991) which contains four items (e.g., “Using [the IT innovation] is compatible with all aspects of my work”, “Using [the IT innovation] fits into my work style”). These are rated on a 7-point Likert scale, from Extremely disagree to Extremely agree, and averaged to produce the subscale score. A minimum average score of 5.5 is the threshold set for compatibility.

In addition, a 4-item scale, the Appropriateness of Intervention Measure (Weiner et al., 2017), will be completed by all participants. Example items include “This [evidence-based practice] seems fitting” and “This [evidence-based practice] seems like a good match.” Items are scored on a five-point scale of agreement, from 1 = Completely disagree to 5 = Completely agree and averaged for a total score. An average score of at least 4 will indicate adequate appropriateness with this instrument.

### *Feasibility*

Feasibility relates to the extent to which our I-Score intervention is successfully used or carried out within the study site (Proctor et al., 2011). To determine feasibility, data will be collected on the Consent rate, defined as the proportion of approached eligible patients and physicians who consent to participate. Individuals who choose not to participate will be asked to provide select sociodemographic information (sex, year of birth, preferred language) and their reason(s) with a checklist on a refusal form (see the Appendix). If 70% or more agree to participate, the study will be judged feasible on this aspect. We will also examine the Retention rate, indicated by the proportion of patients and physicians who complete the study. Eighty percent will be considered the benchmark for success. Missing I-Score data rates due to network failure as well as patient and provider non-completion of self-reported questionnaire data will be calculated as well. The criterion for success on this metric is at least 90%. Furthermore, participants will complete the Feasibility of Intervention Measure (Weiner et al.,

2017), at T1, T2 and T3, a four-item self-report measure that is appropriate for different stakeholder groups (e.g., patients, providers). Example items include “This [evidence-based practice] seems possible” and “This [evidence-based practice] seems doable.” Average scores of at least 4, indicative of agreement on the 5-point response scale, will signify the I-Score intervention’s feasibility.

